### Trial status and project duration

The trial is scheduled to recruit 44 patients and is currently recruiting. The projected duration for the study is 3 years. The time line is outlined in Table 6.

### Stereotactic radiosurgery

SRS will be delivered utilizing gamma knife or linear accelerator-based techniques. With the Leksell Gamma Knife Perfexion®, Leksell GammaPlan® will be used to generate the treatment plan with respect to the head frame coordinate system created by localization. Target volume and isocenter determination will be based on a brain MRI with the patient’s head in the stereotactic frame. Linear accelerator based stereotactic localization will be performed using the Encompass® SRS thermoplastic mask immobilization system. The patient will undergo a 1 mm slice thickness helical CT scan that will be fused with the MRI brain T1-weighted post-contrast axial scan used for target delineation. The CT-MRI fusion maximum correlation error must be less than 1.5 mm.

The prescribed dose will be based on tumor diameter per RTOG 90–05 dosing criteria with the exception that the largest lesion diameter to be treated with 15 Gy will be 5 cm (Table 5). [27] Since it has been shown that brain metastases up to 4.5 cm can be safely treated with 15 Gy SRS either alone or with WBRT with no reported toxicity at 2–3 months following treatment. [30]

**Table 5 Tab5:** Radiosurgery dose criteria

Maximum Tumor Diameter	Prescribed Dose
≤ 20 mm	24 Gy
21–30 mm	18 Gy
31–40 mm	15 Gy
40–50 mm	15 Gy

SRS will be delivered to each lesion that has not previously undergone treatment. Due to the volumetric summation constraint for the remaining metastases, no single, non-resected lesion greater than 4 cm will be allowed in the study. If any two lesions are within 0.8 to 2 cm of each other, the intervening midplane dose will not exceed 13 Gy. This may require treating each respective target with a lesser dose than dictated by the above dosing criteria to minimize toxicity. The dose to the critical structures, including optic pathway, brainstem, cochlea and medulla, must meet constraints as designated by Task Group 101. [31] If the above constraints cannot be met utilizing the prescribed radiosurgery dose, then the highest dose to the target volume will be used such that constraints can be met. This will be considered a minor deviation.

### Surgical resection

At least one of the 4 lesions has to be either larger than 3 cm or symptomatic to meet the surgical resection criteria. One to four days after radiosurgery, the dominant lesion(s) will be maximally resected and labeled tissue will be sent to the neuropathology department for clinical diagnosis and radiobiological correlative studies. If for safety concern or other considerations, gross total resection is not reached, the residual disease in the setting of subtotal resection will be closely observed given that it has been treated with a definitive dose of SRS, reserving salvage local therapy for cases of progression. [29] Patients who received subtotal resection will be recorded and analyzed as well for risk stratification.

### Correlative analysis

For the radiobiological studies, tissues will be examined for a) pathologic diagnosis b) immunohistochemistry for immune cell infiltrates and c) mitochondrial histochemistry to address DNA damage. In addition, to understand the effect of radiation dosing on tumor tissue at the molecular level, RNA and DNA sequencing will be performed on peripheral and central sites from the tumor specimen of each patient’s tumor samples. The early cellular gene expression changes in response to high dose radiation will be assessed. DNA sequencing and RNA expression will also be correlated with all clinical outcomes to establish prognostic molecular classifications. Protein analysis for apoptotic pathway activation will also be done on tumor cells to assess radiation induced tumor cell killing.

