### Study population

Patients with 1–4 metastatic lesions in the brain identified on a diagnostic brain MRI or CT with at least one meeting the criteria for surgical resection i.e. symptomatic or size > 3 cm, will be identified as potential study candidates. Amongst the study candidates, patients meeting the inclusion and exclusion criteria (Table 4) will be eligible to enroll in the study. Eligible patients who complete the Informed Consent Process will be registered in the OnCore® database and assigned a patient ID number for the clinical study.

**Table 4 Tab4:** Inclusion and Exclusion Criteria

Inclusion Criteria	
1. Radiographically confirmed solid tumor brain metastases 2. Criteria for surgical resection of at least one metastasis per neurosurgeon discretion 3. A diagnostic MRI Brain or CT Head demonstrating the presence of 1–4 solid tumor brain metastases and lesion to be resected no more than 5 cm in any direction, performed within 30 days prior to stereotactic radiosurgery. If multiple lesions are present, then the total brain metastases volume can be no more than 30 cm^3^ excluding the lesion to be resected. 4. For known primary, ds-GPA estimated median survival no less than 6 months 5. For unknown primary, GPA estimated median survival no less than 6 months 6. Surgical candidate per neurosurgeon discretion 7. Surgical resection able to be performed within 1–4 days after radiosurgery 8. Stereotactic radiosurgery candidate per radiation oncologist 9. ≥ 18 years old at the time of informed consent 10. Ability to provide written informed consent and HIPAA authorization 11. Platelet count > 100 k/ml, Hgb > 7.5 g/dL, INR < 1.3, ANC > 1.5 k/ml 12. Patients currently on cytotoxic chemotherapy or immunotherapy are eligible, not including anti-VEGF therapy	
Exclusion Criteria	

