### Response and progression assessment in neuro-oncology brain metastases (RANO-BM) [32]

Following delivery of SRS and surgical resection, all patients will be assessed for their clinical performance status (GPA/ds-GPA/ ECOG performance status/KPS) as well as toxicity at follow-up intervals as detailed in Table 6. Serial MRIs will be analyzed per RANO-BM criteria for assessment of LC, DBF and cranial progression free survival. [32] Initiation or continuation of chemotherapy, immunotherapy or other systemic agents is allowed per medical oncologist discretion.

**Table 6 Tab6:** Study Protocol and follow up timeline

	Screening (within 30 days of SRS)	Stereotactic radiosurgery	Surgery (1–4 days post SRS)	1 Month Follow Up^a^ (30 days post SRS)	Follow Up^b^ (every 3 m until 2 yrs)	Long Term Follow Up^c^ (> 2 yr. post SRS)
Radiation oncology consult	x					
Neurosurgical consult	x					
Medical History	x			x	x	x
Physical Examination	x			x	x	x
Vitals	x	x	x	x	x	x
ds-GPA/GPA/ECOG performance status/KPS	x			x	x	x
Diagnostic MRI Brain or CT Head	x					
MRI Brain Planning Scan^f^		x				
WBC, Hgb, platelets, INR, ANC^d^	x		x			
Urine pregnancy test	x					
Toxicity assessment				x	x	
MRI Brain^e^					x	x
Tissue collection			x			

^a^Variations of +/− 14 days from the scheduled visit are permitted

^b^Variations of +/− 30 days from the scheduled visit are permitted

^c^Subjects will be followed at physician’s discretion, approximately every 6 months after 2 years post SRS, per standard of care. Any MRI Brain, physical exam or vitals obtained at these appointments will gathered. However, if these procedures are not performed per standard of care, this will not be a deviation

^d^Repeating Hgb, platelets, INR and ANC at time of surgery is per discretion of neurosurgeon

^e^MRI Brain performed at Indiana University will have sequences including contrast, no contrast, FLAIR, DTI and PWI. If patient receives MRI Brain outside of Indiana University, a minimum of contrast, no contrast and FLAIR will need to be obtained and all sequences mentioned above are encouraged

^f^Variations of −30 days from the scheduled visit are permitted for linear accelerator based SRS, and may include the baseline screening MRI at the treating radiation oncologist’s discretion

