### Statistical analysis

A sample size of 44 patients will provide 82% power with an alpha = 0.05 to determine if the proportion of patients with local control at 6 months is <= 83% or > = 95%. For the primary objective of 6-month local control for pre-operative SRS followed by surgical resection of the brain metastases, the proportion of patients who have local control at 6 months will be calculated along with a 95% confidence interval. Testing the observed proportion against a baseline 6-month local control proportion of 83% at a one-sided alpha of 5% using a binomial test will be done. The proportion of patients who have in-brain distant failure, radiation necrosis, and leptomeningeal spread in the evaluated patients will be summarized and exact binomial 95% confidence intervals will be determined. Additionally, time to local failure, distant in-brain progression, and overall survival will be calculated and analyzed using Kaplan-Meier methods with the medians estimated with a 95% confidence interval. The probability rates will be provided for 6 months, 1 year, and 2 years. Finally, the tissue biomarkers of interest in the molecular study will be correlated with treated lesion location, in-brain local control, in-brain distant control, and overall survival using Cox proportional hazards regression. Time dependent ROC curves will be generated to assess predictive ability.

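### The marker analysis seeks prognostic classes across mixed primaries but names no adjustment for, or comparison with, the baseline ds-GPA/GPA already recorded

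*Protocol article*

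**What the plan says.** Table 4 of the protocol article (Study population) admits radiographically confirmed brain metastases from any solid tumour and does not restrict the primary. Prognosis at entry is judged by diagnosis: "For known primary, ds-GPA estimated median survival no less than 6 months", with a matching 6-month rule on GPA when the primary is unknown. Table 6 lists "ds-GPA/GPA/ECOG performance status/KPS" at screening and at each follow-up visit. Pathologic diagnosis of the resected tissue is also obtained (Correlative analysis).

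The aim of the sequencing work appears in Correlative analysis: "DNA sequencing and RNA expression will also be correlated with all clinical outcomes to establish prognostic molecular classifications". The Statistical analysis section supplies the method. Tissue biomarkers are related to lesion location, local control, distant control and overall survival by Cox regression, and "Time dependent ROC curves will be generated to assess predictive ability". No covariate, stratum or clinical comparator is named in either section.

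The molecular objectives are listed as exploratory (Exploratory objectives, and the end of Background).

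**The concern.** By using a diagnosis-specific score for eligibility, the trial accepts that expected survival depends on the primary. If a molecular marker also differs by primary, it will be associated with survival through tumour type alone, even when it carries no information within a tumour type. A Cox model without a prognosis term cannot separate the two, and an AUC with no comparator does not show whether the marker adds anything to a score the clinician already has.

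The stake is how the exploratory results are read. The article speaks of establishing classifications, and the Discussion suggests that the molecular work may help identify patients who need further treatment after surgery. A relabelled tumour type would be a poor basis for either.

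**Working it through.** **1. The plan's own figure.** The Statistical analysis section states: "A sample size of 44 patients will provide 82% power with an alpha = 0.05", for 83% against 95%, tested "at a one-sided alpha of 5% using a binomial test". With X ~ Binomial(44, p), the smallest cut-off r with P(X ≥ r | 0.83) ≤ 0.05 is r = 41:
- P(X ≥ 41 | 0.83) = 0.0450
- P(X ≥ 41 | 0.95) = 0.8235

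The stated 82% is reproduced. No event count or power is stated for the marker analysis, so nothing stated is disputed.

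**2. Size of the spurious effect (assumed inputs).** Take two prognosis classes, 50/50, with class hazard ratio H. The marker is present in a fraction a of the poor class and 1 − a of the good class, and has no effect within class. Among marker-positive patients a fraction a is then in the poor class; among marker-negative patients, 1 − a. The marker's apparent hazard ratio at time zero is

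(aH + 1 − a) / ((1 − a)H + a).

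- a = 0.7, H = 1.5: 1.35/1.15 = 1.17
- a = 0.7, H = 3: 2.4/1.6 = 1.50
- a = 0.9, H = 1.5: 1.45/1.05 = 1.38
- a = 0.9, H = 3: 2.8/1.2 = 2.33

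The median unadjusted hazard ratios in simulation agree: 1.18, 1.54, 1.36 and 2.39.

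**3. How often such a marker is called prognostic, two classes.** Assumptions: 44 patients, overall median about 13 months, 24 months of follow-up, two-sided 5% test, about 1,500 runs per case. Expected deaths with no class difference: 44 × (1 − 2^(−24/13)) = 44 × 0.722 = 31.8; simulated, 31-32.

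| Class HR | Marker 70%/30%: unadjusted, adjusted | Marker 90%/10%: unadjusted, adjusted |
|---|---|---|
| 1.0 | 4.5%, 5.7% | 5.2%, 5.9% |
| 1.5 | 6.6%, 5.7% | 13.1%, 5.9% |
| 2.0 | 11.2%, 5.7% | 32.7%, 6.8% |
| 3.0 | 20.2%, 4.5% | 65.4%, 6.6% |

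**4. Three diagnoses.** Assumptions: 44 patients, exponential survival, follow-up to 24 months, about 30 deaths, 800 runs per case. Marker means differ between diagnoses with an SD of 1 or 2 within-diagnosis SDs. Adjustment is for the log of the true diagnosis median.

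| Medians (months) | Largest HR between diagnoses | Unadjusted (SD 1, SD 2) | Adjusted (SD 1, SD 2) |
|---|---|---|---|
| 10/14/20 | 20/10 = 2.0 | 8.6%, 13.5% | 5.5%, 7.2% |
| 8/14/24 | 24/8 = 3.0 | 19.1%, 22.5% | 5.1%, 6.0% |
| 6.5/14/30 | 30/6.5 = 4.6 | 24.9%, 37.0% | 5.5%, 5.0% |

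A repeat run on these inputs gave about 10-41% unadjusted, 3-6% adjusted for the true diagnosis-level score, and 6-8% when the score carried assumed error. All assumed medians exceed the 6-month entry floor. The central 14 months lies within the 13.9-17.2 months that Table 3 lists for pre-operative SRS.

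**5. Events for local failure.** At the planning values, expected failures by 6 months are 44 × 0.05 = 2.2 to 44 × 0.17 = 7.5. That is too few to carry an added covariate, so the adjustment is proposed for overall survival only.

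**The case against.** A reader might infer that the plan fits these models without ds-GPA. The documents do not say so. Cox regression admits covariates and strata, and a condensed article may leave the covariate list of an exploratory analysis to the full protocol or analysis plan, which are not shown. This objection stands: the text supports only that no adjustment or comparator is named.

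The rest of the opposing case:
- **The work is exploratory.** It claims no error rate, and no trial decision rests on it. This stands and lowers the priority. It does not sit easily with the word used for the aim in Correlative analysis, which is to establish classifications.
- **An unadjusted association is real.** A marker that tracks tumour type is truly associated with survival in a mixed cohort, so calling it false presumes that value beyond diagnosis is the question. This is fair. But for a new molecular classification, value beyond a score already in hand is the useful question, and reporting both answers is easy.
- **The size is assumed.** This stands. The mix of primaries, the markers and the spread of scores are not given, and the 6-month floor narrows that spread without removing it.
- **ds-GPA and GPA are different scores.** This stands, and the fix has to put them on one scale. Adjusting for the true diagnosis median is also the most favourable case; a score with error left 6-8%.

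A reader might also infer that the interval to surgery, "One to four days after radiosurgery", confounds the tissue results by tracking urgency. The documents do not support that link. Nor is a centre-versus-periphery comparison missing: sampling of both sites is planned, and the Discussion states the expected difference.

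**Conclusion.** The point holds as an optional improvement. The article sets a prognostic aim across mixed primaries and attaches a method to it, without naming adjustment for, or comparison with, a baseline score the trial already records. A marker that only identifies the primary could therefore be reported as prognostic.

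The size is illustrative: about 10-40% against a nominal 5% under three diagnoses with assumed medians of 6.5-30 months, and about 7-65% under the two-class assumptions. With no prognostic difference between classes, or no marker difference between diagnoses, the rate stays near 5%. None of these figures is an estimate for this trial. The primary test, its 82% power and N = 44 are unaffected.

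**What to change.** In the Statistical analysis section:
- Fit the overall-survival marker Cox models with baseline prognosis as one covariate. Put ds-GPA (known primary) and GPA (unknown primary) on a common scale. Estimated median survival is the natural choice, since both eligibility rules are already expressed in it.
- Report the gain in time-dependent AUC over that score alone, beside the marker's own AUC.
- Describe the marker results as exploratory and hypothesis-generating, including the local-failure models, which stay unadjusted because events are few. Soften the matching wording in Correlative analysis.

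The change is to wording and analysis only, and the scores are already collected. It uses one degree of freedom in a model with about 30 deaths (assumed). It leaves tumour-type confounding in the local-failure models, which is why the hypothesis-generating label matters there.

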### Response and progression assessment in neuro-oncology brain metastases (RANO-BM) [32]

Following delivery of SRS and surgical resection, all patients will be assessed for their clinical performance status (GPA/ds-GPA/ ECOG performance status/KPS) as well as toxicity at follow-up intervals as detailed in Table 6. Serial MRIs will be analyzed per RANO-BM criteria for assessment of LC, DBF and cranial progression free survival. [32] Initiation or continuation of chemotherapy, immunotherapy or other systemic agents is allowed per medical oncologist discretion.

**Table 6 Tab6:** Study Protocol and follow up timeline

	Screening (within 30 days of SRS)	Stereotactic radiosurgery	Surgery (1–4 days post SRS)	1 Month Follow Up^a^ (30 days post SRS)	Follow Up^b^ (every 3 m until 2 yrs)	Long Term Follow Up^c^ (> 2 yr. post SRS)
Radiation oncology consult	x					
Neurosurgical consult	x					
Medical History	x			x	x	x
Physical Examination	x			x	x	x
Vitals	x	x	x	x	x	x
ds-GPA/GPA/ECOG performance status/KPS	x			x	x	x
Diagnostic MRI Brain or CT Head	x					
MRI Brain Planning Scan^f^		x				
WBC, Hgb, platelets, INR, ANC^d^	x		x			
Urine pregnancy test	x					
Toxicity assessment				x	x	
MRI Brain^e^					x	x
Tissue collection			x			

^a^Variations of +/− 14 days from the scheduled visit are permitted

^b^Variations of +/− 30 days from the scheduled visit are permitted

^c^Subjects will be followed at physician’s discretion, approximately every 6 months after 2 years post SRS, per standard of care. Any MRI Brain, physical exam or vitals obtained at these appointments will gathered. However, if these procedures are not performed per standard of care, this will not be a deviation

^d^Repeating Hgb, platelets, INR and ANC at time of surgery is per discretion of neurosurgeon

^e^MRI Brain performed at Indiana University will have sequences including contrast, no contrast, FLAIR, DTI and PWI. If patient receives MRI Brain outside of Indiana University, a minimum of contrast, no contrast and FLAIR will need to be obtained and all sequences mentioned above are encouraged

^f^Variations of −30 days from the scheduled visit are permitted for linear accelerator based SRS, and may include the baseline screening MRI at the treating radiation oncologist’s discretion

### Leptomeningeal disease and radiation necrosis

Assessment for LMD and RN will be performed using contrast-enhanced MRI scans. LMD is defined as new subarachnoid, ventricular or parenchymal enhancing nodules, focal or diffuse pial enhancement, ependymal, sulcal, folia or cranial nerve enhancement. [33] RN is defined as a contrast-enhancing lesion with surrounding edema within previous radiation treatment fields. MR spectroscopy and perfusion weighted imaging (PWI) sequences will be analyzed to differentiate between RN and recurrent tumor. [34, 35]

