**Methods:**

This prospective, single arm, phase II trial will recruit patients with up to 4 brain metastases and at least one resectable lesion. All lesions will be treated with SRS and symptomatic lesions will be resected within 1–4 days after SRS. Patients will be monitored for 6-month local control, in-brain progression free survival, distant in-brain failure, rate of leptomeningeal spread, radiation necrosis and overall survival. Additionally, we will also perform correlative radiobiological molecular studies to assess the effect of radiation dosing on the tumor tissue and clinical outcomes. We expect that pre-operative SRS to the gross tumor prior to surgical resection will improve local control and decrease leptomeningeal failure.

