The first pre-operative SRS study was published by Asher et al where 47 patients were treated consecutively with neoadjuvant SRS before surgical resection, with 24 of those patients analyzed as part of a prospective trial, and the results showed 6-month and 12-month LC rate of 97.8 and 85.6% respectively (Table 3). [28] Subsequently Patel et al performed a multi-institutional retrospective comparison of outcomes and toxicities for pre-operative SRS compared to post-operative SRS for 180 patients. [29] The planning target volume (PTV) of pre-operative SRS had 0 mm margin expansion from gross tumor volume (GTV) compared to 2 mm margin for PTV of post-operative SRS. The study did not note any statistical difference in the rates of local recurrence, distant brain recurrence, and OS but the pre-operative SRS cohort demonstrated significantly lower rates of symptomatic RN (4.9% vs. 16.4%, *p* = 0.01) and LMD (3.2% vs. 16.6%, p = 0.01) than their post-operative SRS counterpart. [29] The abstract of an updated retrospective analysis of 117 patients with 125 lesions treated with pre-op SRS is now available online (https://www.redjournal.org/article/S0360-3016(18)31346-4/fulltext) and reported the 1 and 2-year cavity LC rate to be 80.1 and 74.9%, distant in-brain failure (DBF): 45.3 and 60.2%, and LMD: 4.3 and 4.3%, respectively. Nevertheless, the results were likely limited by some intrinsic selection bias, as the two retrospective cohort groups were statistically different in their baseline performance status (Figure 1).

**Table 3 Tab3:** Published studies of Pre-op SRS prior to Metastases Resection

Study	Treatment Modalities (Number of patients)	Target	Median survival (months)	Outcomes			
				LR (%)	DBF (%)	LMD (%)	Symptomatic RN (%)
Asher, 2014 [28]	PreOP SRS (47)	GTV = PTV	NA	14.4 (1 yr)	38.2 (1 yr)	NA	NA
Patel, 2016 [29]	PreOP SRS (66) Vs. Postop SRS (114)	GTV = PTV PTV = cavity + 1–2 mm margin	17.1 13.5	15.9 (1 yr) 12.6 (1 yr)	32 (1 yr) 39.1(1 yr)	3.2 (1 yr) 3.2 (2 yr) 8.3 (1 yr) 16.6 (2 yr)	4.9 (2 yr) 16.4 (2 yr)
Patel, 2017 [44]	PreOP SRS (66) Vs. Postop WBRT [36]	GTV = PTV PTV = cavity + 1–2 mm margin	13.9 12.6	24.5 (2 yr) 25.1 (2 yr)	53.2 (2 yr) 45 (2 yr)	3.5 (2 yr) 9 (2 yr)	5.6 (2 yr) 0 (2 yr)
Prabhu, 2018 (Abstract only)	Pre-OP SRS (117)	GTV = PTV	17.2	19.9 (1 yr); 25.1 (2 yr)	45.3 (1 yr); 60.2 (2 yr)	4.3 (1 yr); 4.3 (2 yr)	2.6 (1 yr) 4.8 (2 yr)

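### The leptomeningeal disease definition takes in any new parenchymal enhancing nodule, so an ordinary new brain metastasis could be counted as both distant in-brain failure and leptomeningeal disease

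*Protocol article*

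**What the plan says.** The section on leptomeningeal disease and radiation necrosis gives the operative rule: "LMD is defined as new subarachnoid, ventricular or parenchymal enhancing nodules, focal or diffuse pial enhancement". It then lists ependymal, sulcal, folial and cranial nerve enhancement. The items are alternatives. The section sets no condition on where a parenchymal nodule must lie and does not exclude lesions already scored as distant failure.

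Elsewhere the article treats LMD and DBF as different events:

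- The secondary objectives list them separately, and the abstract names "distant in-brain failure, rate of leptomeningeal spread" as separate items to monitor.
- The eligibility table admits patients with 1-4 brain metastases but excludes those with leptomeningeal metastases.
- DBF has its own instrument: "Serial MRIs will be analyzed per RANO-BM criteria for assessment of LC, DBF and cranial progression free survival". The Follow-up section has LMD read from the same MRIs.
- The Statistical analysis section reports each as its own proportion: "The proportion of patients who have in-brain distant failure, radiation necrosis, and leptomeningeal spread in the evaluated patients will be summarized", with exact binomial 95% confidence intervals.

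The Background also keeps them apart when quoting the literature. For an updated pre-operative series of 117 patients it gives, at one and two years, "distant in-brain failure (DBF): 45.3 and 60.2%, and LMD: 4.3 and 4.3%, respectively". The abstract expects that pre-operative SRS "will improve local control and decrease leptomeningeal failure".

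**The concern.** Every other item in the LMD list concerns the CSF spaces, their linings or surfaces, or the cranial nerves. *Parenchymal* is the exception: it describes brain tissue, where ordinary metastases grow. A reader who follows the written rule must record a new discrete metastasis away from the treated sites as LMD, and RANO-BM also makes it a distant failure.

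At stake is what the LMD proportion means. Lower LMD is one of the two expectations stated in the abstract, and the Discussion repeats it against historical post-operative SRS. In a single-arm trial that contrast can only be made against published rates, so LMD must mean the same thing here as it did there. The error would also run against the trial's own hypothesis.

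**Working it through.** **The plan's own design figure.** The only computed figure is 82% power with 44 patients, 83% against 95%, one-sided 5%, binomial test. The exact rule of at least 41 of 44 with local control gives alpha 0.0450 and power 0.8235. The 82% is reproduced. It concerns local control only and does not involve the LMD definition.

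**Inputs for the LMD question** (Table 3 and Background, one year, pre-operative SRS):

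- Multi-institutional comparison, pre-operative cohort: LMD 3.2%, DBF 32%.
- Updated pre-operative series: LMD 4.3%, DBF 45.3%.

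These come from other cohorts. Using them for this trial is an assumption, as is treating each distant failure as a new enhancing parenchymal nodule.

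**Did the cited series use such a broad rule?** If each new parenchymal nodule had counted as LMD, LMD could not lie below DBF. It does, by a factor of ten (3.2 against 32; 4.3 against 45.3). So these series cannot have counted ordinary new metastases as LMD.

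**Literal reading.** The proportion becomes P(true LMD or new parenchymal metastasis). With L = LMD and D = DBF it is max(L, D) if one event contains the other, 1 − (1 − L)(1 − D) if they are independent, and L + D if they never coincide.

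| Series | L | D | Nested | Independent | Disjoint |
|---|---|---|---|---|---|
| Multi-institutional, pre-op | 3.2% | 32% | 32.0% (10.0×) | 34.2% (10.7×) | 35.2% (11.0×) |
| Updated pre-op series | 4.3% | 45.3% | 45.3% (10.5×) | 47.7% (11.1×) | 49.6% (11.5×) |

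In patients, using the smallest (nested) figures:

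- Intended meaning: 44 × 0.032 = 1.4 to 44 × 0.043 = 1.9.
- Literal meaning: 44 × 0.32 = 14.1 to 44 × 0.453 = 19.9.

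The planned exact 95% interval would be 0.6-15.5% for 2 of 44, 18.6-47.6% for 14 of 44 and 30.4-61.2% for 20 of 44. The first does not overlap either of the others.

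**Partial application.** Let a fraction f of distant failures be coded as LMD, independently of true LMD: 1 − (1 − L)(1 − fD). The values of f are assumptions; the article gives none.

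| Series | f = 10% | f = 25% |
|---|---|---|
| Multi-institutional, pre-op | 1 − 0.968 × 0.968 = 6.3% (2.0×) | 1 − 0.968 × 0.920 = 10.9% (3.4×) |
| Updated pre-op series | 1 − 0.957 × 0.9547 = 8.6% (2.0×) | 1 − 0.957 × 0.88675 = 15.1% (3.5×) |

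Independence matters at the low end. If the patients with true LMD were all among those miscoded, f = 10% would give only 3.2% and 4.5% (almost no inflation), and f = 25% would give 8.0% and 11.3% (2.5- and 2.6-fold).

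**The case against.** The strongest reply is that nobody would read the scans that way. The article separates the two entities in its objectives, eligibility, analysis and literature tables, so readers may well keep ordinary metastases under DBF. This stands as a limit on size: ten-fold needs nearly every distant failure to be coded as LMD, and the true fraction is unknown. It does not rescue the definition, because correct scoring would then depend on judgment that departs from the written rule.

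A second reply is that the article condenses a fuller protocol, and that the source cited for the definition may qualify the term. Neither is at hand. But the point is not a missing detail: the article states a definition, and the definition as stated is too wide.

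Third, LMD is one of five secondary objectives, summarised with an interval and given no test, null value or decision rule. This stands and sets the severity.

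Two stronger readings are tempting and are not supported:

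- A reader might infer that the two endpoints cannot be separated at all. DBF is scored under RANO-BM and is not altered by the LMD wording. Contamination runs one way, into LMD, and re-reading existing scans can undo it.
- A reader might infer that the trial would appear to show worse LMD than post-operative SRS. The article plans no formal comparison. The quoted post-operative rates (8.3% at one year, 13%, 16.6% at two years, 28% at 12 months) come from other cohorts at different horizons, and their LMD definitions are not given. The low literal figure, 32%, is only just above 28% (14.1 against 44 × 0.28 = 12.3 patients). With partial miscoding the result falls below several of these rates.

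**Conclusion.** The definition is wrong as written: a new discrete parenchymal metastasis meets it, although the article treats such a lesion as a different event. Under literal use, with the cited one-year pre-operative rates carried over to all 44 patients, LMD could be recorded in about 14-20 patients instead of 1-2. This roughly ten-fold figure is an upper case for scoring at that horizon. If 10-25% of distant failures were coded as LMD, independently of true LMD, the inflation would be about 2- to 3.5-fold. The Statistical analysis section names no time point for the LMD proportion, so the one-year horizon is itself an assumption.

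The overlap in wording is certain; its size depends on how readers apply it. It affects the descriptive secondary LMD proportion and any informal comparison with published rates. DBF, 6-month local control and the 82% power are untouched. Severity: should-fix, on a secondary endpoint.

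**What to change.** Delete *parenchymal* from the LMD definition, or restrict it to nodules contiguous with the pia, ependyma or subarachnoid space. Add that a discrete new parenchymal metastasis counts as distant in-brain failure only, and that a patient is counted for both events only when each definition is met separately. Apply the same rule to scans already scored, before LMD is tabulated.

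The cost is a one-sentence clarification and a re-read of scans already scored. No new data are needed, and the sample size and primary analysis do not change.
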